#### Secondary outcomes

Unpaired t-tests will be used to compare mean knowledge scores at follow-up. Fisher’s exact test will be used to compare proportions of sufficient knowledge after counselling and at follow-up. Participants will be rated as having sufficient knowledge if they correctly answered at least 8 out of 12 questions. Unpaired t-tests will be used to compare average individual differences between planned and achieved values of blood pressure and HbA1c. Fisher’s exact tests will be used to compare the groups regarding rates of individual goal achievement (yes/no): statin choice, smoking status, blood-pressure (defined as reaching 80% to 120% of the goal), and HbA1c (defined as reaching 80% to 120% of the goal). Mann Whitney U-Test will be used to compare the medication uptake from T1 to T2 (increase/unchanged/decrease).

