## Objectives

Primary objective is to investigate if the ISDM programme is superior to the control-intervention regarding patients’ knowledge and realistic expectations concerning benefits and harms of the available treatment options. Key secondary objective is to determine if patients in the ISDM group achieve their individual treatment goals better than patients in the control-group. Additional objectives are to assess if patients presenting high numeracy levels achieve better knowledge than patients presenting low numeracy, if social status correlates to the level of knowledge, and if patients with good knowledge achieve their treatment goals better than patients with poor knowledge.

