### Study interventions

#### Intervention group (ISDM programme)

The intervention (Table 1) comprises a decision aid booklet [17] and a corresponding counselling module. The counselling is provided by diabetes educators of the participating clinic. Patients are guided through the decision making process, by 1) jointly assessing the patient’s individual heart attack risk, 2) providing outcome probabilities of the available preventative treatment options, and 3) supporting to set individual goals regarding smoking cessation, glucose control, blood pressure control, and statin treatment. A physician is to be consulted if patients wish a change of treatment regimens.

**Table 1 T1:** Characteristics of intervention and control intervention

	**ISDM programme**	**Control-intervention**
**Components**	Decision aid booklet “On the prevention of heart attack in type 2 diabetes” [17]	Brochure “Stress” [27]
	Curriculum	Curriculum
	Media: Specific wall charts, worksheets, question cards, and a magnet board	Media: Specific wall charts, worksheets, and a relaxation exercise
**Duration**	60-90 minutes	60-90 minutes
**Group size**	4 participants	4 participants

The counselling module takes about 90 minutes. Patients are asked to read and work through the DA, at least one week before the group counselling session.

For study purposes, two diabetes educators have attended the ISDM programme specific train-the-trainer module given by a research fellow of the Unit of Health Sciences and Education of the University of Hamburg. In order to ensure educational fidelity, certified diabetes educators provide the counselling sessions. To ensure fidelity of the evidence-based contents, the sessions are videotaped and analysed. If required, the research fellow gives feedback for optimisation.

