#### Control group

Framing, duration and structure of the control-intervention are similar to the ISDM intervention (Table 1). In contrast to the ISDM intervention, participants are guided through a counselling session about nutrition, sports, and stress coping. The session ends after a take home relaxation exercise. At least one week before the session, all participants receive a brochure on stress management offered by health insurances [27].

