### Outcomes

Primary outcome measure (Table 2) is the level of patient knowledge relating to the concept of risk, the notion of heart attack risk, and the benefits and harms of preventative treatment. Knowledge is captured by a standardised questionnaire consisting of 12 questions to assess *comprehension of risk information* and *realistic expectations*[28], plus one question to assess *numeracy*[29].

**Table 2 T2:** Data collection

**Outcomes**	**Measures**	**No. of items**	**Follow-up**^ ***** ^
Knowledge	• Questionnaire developed on the basis of Bloom’s taxonomy [30] and evidence-based information on heart attack prevention in type 2 diabetes [17] (updated 08/2012)	13	T1, T2
Realistic expectations	• Questionnaire developed on the basis of ISDM-counselling	6^**^	T1, T2
Numeracy	• Numeracy test (one minute test for general population) [29]	1^***^	T1
Treatment goals	• Statin medication, levels of blood pressure and glucose control, smoking, and patient’s prioritized treatment goal are documented on a standardised form	1 for each goal	T1
Achievement of treatment goals	• Statin medication (patient medication boxes)	1	T2
	• Blood pressure (self-monitoring, standardised measure if not available)	1	T2
	• HbA1c-level (standardised measure)	1	T2
	• Smoking cessation (question by diabetes educator)	1	T2
Medication	• Variation in medication intake (statins, antihypertensive drugs, glucose-lowering agents) are documented using medical records (T1) and by verifying patients’ pill-packages (T2).	3	T1, T2

^*^ T1; at the end of the counselling session; T2; at 6 months follow-up.

^**^ 6 out of 13 questions of the knowledge test.

^***^ 1 out of 13 questions of the knowledge test.

Secondary outcome measures comprise 1) sustainability of knowledge; 2) achievement of individual treatment goals regarding the use of statins, levels of blood pressure and glucose control, and smoking; 3) achievement of treatment goals prioritised by the individual patients; 4) medication uptake from T1 to T2.

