### Data collection

The EPRS of the clinic and standardised forms are used to collect baseline characteristics and outcome measures.

Baseline characteristics include age, gender, first-language, social status [31], smoking status, blood pressure, LDL-cholesterol, total cholesterol, HbA1c, current medication, and previous participation in diabetes patient education programmes.

Baseline risks of myocardial infarction are calculated by using a risk assessment tool based on age, smoking status, and clinical parameters. The tool is derived from the Framingham function and calibrated [32] to the average heart attack risk in the German population.

Knowledge is assessed directly after the counselling session and at 6 months follow-up. The individual treatment goals regarding smoking cessation, glucose control, blood pressure control, and statin treatment are assessed after the counselling session. Achievement of treatment goals is assessed during a consultation at 6 months follow-up. Current medication is monitored by verifying patients’ pill-packages. Smoking status is assessed by using a standardised interview question. Current blood pressure values (mean of 2 weeks) are extracted from patient diaries. If values are not available, blood pressure is measured before counselling by a nurse applying a standardised procedure (after 5 minutes seated position). Glucose control is assessed by measuring HbA1c-levels [33].

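### The t-test on planned versus achieved HbA1c and blood pressure does not cleanly measure goal achievement: read as signed, misses cancel, and a difference in goals chosen after counselling can by itself give a significant result.

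*Protocol article*

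**What the plan says.** All references are to the protocol article.

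- **Test.** Secondary outcomes: "Unpaired t-tests will be used to compare average individual differences between planned and achieved values of blood pressure and HbA1c". The text does not say whether the difference is signed or absolute.
- **When the goal is fixed.** Data collection: "The individual treatment goals regarding smoking cessation, glucose control, blood pressure control, and statin treatment are assessed after the counselling session". The footnote to Table 2 defines the time points: "T1; at the end of the counselling session; T2; at 6 months follow-up". The goal is a T1 value and the achieved level a T2 value.
- **Who is helped to set goals.** The third step of the ISDM counselling is "supporting to set individual goals regarding smoking cessation, glucose control, blood pressure control, and statin treatment". In the control arm, "participants are guided through a counselling session about nutrition, sports, and stress coping". No support for setting these goals is described there, although the planned tests compare goal achievement between the groups.
- **Purpose.** Objectives: "Key secondary objective is to determine if patients in the ISDM group achieve their individual treatment goals better than patients in the control-group".
- **Companion endpoint.** The same section plans Fisher's exact tests on a yes/no outcome, in which blood pressure and HbA1c count as achieved within 80% to 120% of the goal.
- **Baseline.** The characteristics collected include "blood pressure, LDL-cholesterol, total cholesterol, HbA1c, current medication". Secondary outcomes names no between-arm comparison of achieved HbA1c or blood pressure, or of their change from baseline.

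**The concern.** There are two separate problems.

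The first depends on how the sentence is read. If the difference is signed, a patient one point above goal and a patient one point below average to zero, the same as two patients exactly on goal. The mean then shows whether an arm lies above or below its goals on average, not how well patients met them.

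The second does not depend on the sign. The goal is a post-randomisation quantity that the ISDM programme is designed to influence. If counselling leads patients to choose different goals, the endpoint moves even when HbA1c and blood pressure are the same in both arms. A significant result could reflect different goals, different outcomes or both, and the planned tests do not show which. At stake is the interpretation of one of the analyses that serve the key secondary objective.

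**Working it through.** **Inputs from the protocol article.** Two-sided 5% level and 64 analysed patients per group (Sample size). That figure was set for the knowledge outcome and is borrowed here. It reproduces: 2 × (1.96 + 0.842)² × 0.4² / 0.2² = 62.8, so 63 by the normal approximation, and 63.8, so 64, by the exact t-test. The document gives no SD, power or goal values for HbA1c or blood pressure.

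**Assumptions, for illustration only.**
- HbA1c: achieved mean 7.4 (SD 0.8) in both arms; goal mean 7.0 (SD 0.5); goal-achieved correlation 0 or 0.5.
- Blood pressure: achieved mean 138 (SD 12) in both arms; goal mean 135 (SD 8); correlation 0.
- Only the ISDM goal is shifted.

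**Step 1: the contrast.** Let A be the achieved value and G the goal. Then

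mean(A − G) in ISDM minus mean(A − G) in control = (difference in mean A) − (difference in mean G).

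With equal achieved values this is the goal difference with its sign reversed. No assumption is needed.

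**Step 2: rejection rate of the signed test from a goal shift alone.** The SD of A − G is √(0.5² + 0.8² − 2 × ρ × 0.5 × 0.8), which is 0.943 at ρ = 0 and 0.70 at ρ = 0.5. For blood pressure it is √(8² + 12²) = 14.4. The rejection rate is about Φ(shift/SD × √(64/2) − 1.96). The simulation used 10,000 trials per row.

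| Goal shift | SD | shift/SD × 5.657 | Approximation | Simulated |
|---|---|---|---|---|
| HbA1c 0.25 | 0.943 | 1.50 | 32% | 32% |
| HbA1c 0.25 | 0.70 | 2.02 | 52% | 51% |
| HbA1c 0.5 | 0.943 | 3.00 | 85% | 84% |
| HbA1c 0.5 | 0.70 | 4.04 | 98% | 98% |
| Blood pressure 5 mmHg | 14.4 | 1.96 | 50% | 50% |
| Blood pressure 10 mmHg | 14.4 | 3.92 | 97% | 97% |

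A t-test on the achieved values rejected in about 5% of trials throughout.

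**Step 3: cancellation under the signed reading.** Deviations from goal have mean 0 in both arms, with SD 1.0 in one and 0.3 in the other (mean absolute miss 0.80 against 0.24). The signed test rejects in 5% of trials and the absolute-distance test in 100%. The signed test does not see that one arm misses by more than three times as much.

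**Step 4: does the absolute distance remove the goal-shift problem?** It reduces it but does not remove it. With the less strict ISDM goals of Step 2, the absolute test rejects in 8% to 15% of trials (0.25 points) and 9% to 17% (0.5 points). These low rates depend on direction. A goal 0.5 points stricter raises the mean gap from 0.4 to 0.9. By the folded-normal mean, σ√(2/π)exp(−μ²/2σ²) + μ(1 − 2Φ(−μ/σ)), the mean absolute distance then rises from 0.82 to 1.07 at σ = 0.943, and from 0.65 to 0.97 at σ = 0.70. In a further simulation of the same size the absolute test rejected in 54% to 91% of trials for that shift, and in 15% to 32% for a goal 0.25 points stricter.

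**Step 5: the binary endpoint.** Misses cannot cancel in the 80% to 120% band, but it uses the same T1 goals. A goal 0.5 points less strict raises the share within the band from 82% to 89% (ρ = 0) or from 91% to 97% (ρ = 0.5), with identical achieved values.

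**Step 6: gain from baseline adjustment.** With baseline-to-T2 correlation r, ANCOVA removes r² of the variance: 0.5² = 25% and 0.7² = 49% (correlations assumed).

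**The case against.** **The text does not say signed.** This is correct. Signed is the ordinary reading of an average of individual differences, but a statistical analysis plan that is not shown could define absolute deviations. The cancellation point therefore holds only on that reading. The goal-shift point does not depend on it (Step 4).

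**The binary endpoint already covers two-sided misses.** This stands for cancellation. It does not answer the goal shift, because the band is built on the same post-counselling goals (Step 5).

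**Goal concordance is what the trial set out to measure.** This is the strongest reply. The objective is better achievement of individual goals, the programme aims to realign unrealistic expectations, and more realistic goals that are then met may be an intended benefit. It follows that the goal-based endpoint should stay, and that a benefit on it should not be made conditional on lower HbA1c or blood pressure. A patient who makes an informed choice of a less strict goal and meets it is a success under the stated objective. The reply does not remove the need to show goals and outcomes separately.

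**An unadjusted t-test in a randomised trial is valid.** Agreed. Baseline adjustment is proposed for precision, within a comparison of achieved values that the article does not name.

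**Stronger readings that a reader might infer.** One is that the protocol presents this t-test as evidence of better HbA1c or blood pressure control; it nowhere says so. Another is that the programme will shift goals by a known amount or in a known direction; the document gives neither.

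**Conclusion.** The concern holds in a limited form. As ordinarily read, the mean signed difference does not measure goal achievement, because misses in opposite directions cancel. Under either reading the endpoint mixes the goals chosen after counselling with the values achieved, and no planned between-arm test separates them.

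The algebra in Step 1 is exact. The rates of 32% to 98% for HbA1c goal shifts of 0.25 to 0.5 points, and of 50% and 97% for blood pressure shifts of 5 and 10 mmHg, are illustrations under assumed means, SDs, correlations and shifts. They do not predict what this trial will show, and they are not type I error rates for the goal-concordance question. They are the chance of a significant result that would be misread as an effect on HbA1c or blood pressure.

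The consequence is confined to a supporting analysis of a secondary outcome. The primary knowledge outcome and the sample size are not affected. The change is worth making before analysis but does not threaten the trial.

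**What to change.** 1. State that the continuous endpoint is the absolute distance between achieved value and goal. This matches the protocol's own two-sided band. A one-sided shortfall, max(0, achieved − goal), is not a good substitute: under the assumptions above, less strict goals alone make it significant in about 27% to 44% of trials (0.25 points) and 75% to 95% (0.5 points), and it counts every value below goal as a full success.
2. Report the mean and spread of goals, and of achieved HbA1c and blood pressure, by arm. Because the absolute distance still contains the goal, this table is needed to interpret it.
3. Add a supporting ANCOVA of T2 HbA1c and of T2 blood pressure on arm, with the baseline value as covariate.
4. State that the goal-distance result is read as goal concordance and the ANCOVA as the comparison of achieved levels. Neither is a condition for reporting the other.

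The cost is a few sentences of analysis text and a little more secondary analysis. Goals, baseline values and T2 values are already collected, so no visit, measurement or patient is added.

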**Methods/Design:**

A single blinded randomised-controlled trial is conducted to compare the shared decision making programme with a control-intervention. The intervention consists of an evidence-based patient decision aid on the prevention of myocardial infarction and a corresponding counselling module provided by diabetes educators. Similar in duration and structure, the control-intervention targets nutrition, sports, and stress coping. A total of 154 patients between 40 and 69 years of age with type 2 diabetes and no previous diagnosis of ischaemic heart disease or stroke are enrolled and allocated either to the intervention or the control-intervention. Primary outcome measure is the patients’ knowledge on benefits and harms of heart attack prevention captured by a standardised knowledge test. Key secondary outcome measure is the achievement of treatment goals prioritised by the individual patient. Treatment goals refer to statin taking, HbA1c-, blood pressure levels and smoking status. Outcomes are assessed directly after the counselling and at 6 months follow-up. Analyses will be carried out on intention-to-treat basis. Concurrent qualitative methods are used to explore intervention fidelity and to gain insight into implementation processes.

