### Eligibility and recruitment

Patients with type 2 diabetes between 40 and 69 years of age are eligible for enrolment if they have no previous diagnosis of ischaemic heart disease (ICD I20-I25) or stroke (ICD I63) and have participated in the DMP education programmes for patients with type 2 diabetes. Patients are eligible with HbA1c-values between 6 and 9%. This range of values is sensitive to patient participation in decision making, regarding micro-vascular prevention. Patients are excluded if they have proliferative retinopathy, chronic kidney disease stage 3 or higher [26], metastatic cancer, or are addicted to alcohol or cared by a legal guardian.

EPRS is screened for eligible patients (study flow Figure 1). Those are asked to participate during their regular consultation. The first patient was enrolled in March 2013. Estimated completion of recruitment is December 2013.

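### The comparisons of HbA1c and blood pressure against individual goals leave out the baseline values already collected; adjusting for them is a nearly free, modest gain in precision

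*Protocol article*

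**What the plan says.** Under Secondary outcomes, the protocol article fixes the continuous analysis by name: unpaired t-tests on "average individual differences between planned and achieved values of blood pressure and HbA1c". Goal achievement as yes/no is compared with Fisher's exact test. For blood pressure and HbA1c, achievement means ending within 80% to 120% of the goal. Neither test takes a covariate.

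The Data collection section lists the baseline values of both measures: "smoking status, blood pressure, LDL-cholesterol, total cholesterol, HbA1c, current medication". The Data synthesis section uses baseline characteristics for description only.

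The planned value comes from after the session: "The individual treatment goals regarding smoking cessation, glucose control, blood pressure control, and statin treatment are assessed after the counselling session". The achieved value comes later: "Achievement of treatment goals is assessed during a consultation at 6 months follow-up".

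The Randomisation and blinding section describes blocks of 8 and mentions no stratification by HbA1c or blood pressure. On entry, "Patients are eligible with HbA1c-values between 6 and 9" per cent.

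**The concern.** Where a patient stands against a goal at 6 months can depend on where that patient started. The entry range for HbA1c is three percentage points wide, and no balancing on it is stated. If the deviation from the goal is correlated with baseline, an unadjusted comparison carries variance that a covariate would remove, and a chance difference in baseline means moves the estimate.

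The only sample size calculation is for the knowledge test. The HbA1c and blood pressure comparisons take whatever precision that number of patients gives, so efficiency matters here. The choice of test is stated outright, so it is not a detail left to a fuller analysis plan.

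**Working it through.** **The plan's own figure.** For knowledge, with a difference of 0.20, SD 0.4, 80% power and two-sided 5%, the normal approximation gives 2 × (1.96 + 0.84)² × 0.4² / 0.2² ≈ 63 per group. The exact t-test gives 63.8, so 64 per group and 128 in all, as stated. Allowing for 15% drop-out, 128 / 0.85 gives 151, or 152 with 76 per arm. The stated 154 is close to this. Nothing below affects that calculation.

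**Inputs for the check.** From the document: 64 analysed per group and two-sided 5%. Assumed, because the document is silent:
- correlation ρ between baseline and 6-month value, 0.3 to 0.7;
- slope λ of the goal on the patient's baseline, from 0 (one goal for everyone) to 1 (goal is baseline plus a constant);
- equal SDs at baseline and 6 months;
- no other variation in goals;
- an illustrative arm effect of 0.4 SD of the deviation.

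**Formulas.** Let D be achieved minus planned, in units of the 6-month SD.
- Var(D) = 1 + λ² − 2λρ
- corr(baseline, D) = (ρ − λ) / √Var(D)
- adjusted variance / t-test variance = 1 − corr²
- power = Φ(0.4 / √(ratio × 2/64) − 1.96)

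For example, ρ = 0.7 and λ = 0 give a ratio of 1 − 0.49 = 0.51. With ρ = 0.5 and λ = 0.5 the numerator ρ − λ is 0 and the ratio is 1.00.

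**Results: variance ratio (adjusted power).** Unadjusted power is 0.62 in every cell, because the effect is scaled to the SD of D.

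| ρ | λ = 0 | λ = 0.5 | λ = 1 |
|---|---|---|---|
| 0.3 | 0.91 (0.66) | 0.96 (0.64) | 0.65 (0.80) |
| 0.5 | 0.75 (0.74) | 1.00 (0.62) | 0.75 (0.74) |
| 0.7 | 0.51 (0.89) | 0.93 (0.65) | 0.85 (0.69) |

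The variance reduction runs from 0 to 49%. If goals also vary for reasons unrelated to baseline (SD 0.3 on the same scale), the largest reduction falls to 45% (ratio 0.55).

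**Chance imbalance.** The standard error of the difference in baseline means is √(2/64) = 0.177 SD, so gaps up to 1.96 × 0.177 = 0.35 SD lie within the 95% range. A gap shifts the unadjusted contrast by (ρ − λ) × gap. For a gap of 0.2 SD this is +0.14 SD at ρ = 0.7, λ = 0; zero where λ = ρ; and −0.14 SD at ρ = 0.3, λ = 1. If the HbA1c SD is assumed to be 0.8 points, the standard error is 0.8 × 0.177 = 0.141 points, and a gap above 0.2 points in either direction has probability 0.157.

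**The yes/no outcome.** For arithmetic only, a goal of 7.0% gives an achievement band of 5.6% to 8.4%. That band covers 2.4 of the 3 points of the entry range. A goal of 7.5% gives 6.0% to 9.0%, the whole entry range. Non-achievers of the HbA1c goal may therefore be few.

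**The case against.** The strongest reply is that each patient is measured against an individual goal, and in the intervention arm the goal follows a joint look at the patient's own risk. If goals partly follow the starting level, baseline is already partly in the outcome. This stands: in the middle column of the table the gain is 0 to 7%. But zero gain requires λ = ρ, and nothing in the document points to that particular value. With near-equal arms, linear adjustment does not lose large-sample precision elsewhere.

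A reader might also infer more than the document supports:
- *That raw 6-month values are compared.* They are not. The tests are on deviations from a goal.
- *That a sizeable gain is assured.* Looking only at one common goal or at goals fully tied to baseline hides the cases in between, where it can vanish.
- *That a baseline gap passes in full into the result.* Only the fraction ρ − λ does, and its sign can reverse.
- *That the t-tests are invalid.* Randomisation protects the type I error. The issue is precision, and the estimate given a particular imbalance.
- *That the key secondary outcome itself is analysed this way.* The abstract says "Key secondary outcome measure is the achievement of treatment goals prioritised by the individual patient", and the Outcomes section lists prioritised goals separately from individual goals. The Objectives section words the aim more broadly, so the continuous deviations belong to the key secondary outcome only loosely.
- *That no prognostic factor is balanced by design.* The article states no stratification, but it is a condensed account.

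**Conclusion.** The point holds as a modest efficiency improvement to secondary analyses. The plan fixes unadjusted t-tests although the baseline values of the same measures are on its list of collected data. Under the stated assumptions adjustment removes between none and 49% of the variance. At the illustrative effect, power goes from 0.62 to between 0.62 and 0.89. These figures show a range and do not predict a result, since the document gives no correlation, SD, effect or goal slope for HbA1c or blood pressure. The calculation also assumes that 64 patients per arm contribute at 6 months.

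The primary analysis and the sample size are unaffected. Adjustment also leaves a separate weakness in place: the planned value is set after the session, hence after randomisation, so the intervention can alter the goal itself.

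**What to change.** In Secondary outcomes, replace the two unpaired t-tests on planned versus achieved values by a linear model (ANCOVA) with arm and the patient's baseline value of the same measure: HbA1c for HbA1c, blood pressure for blood pressure. Report the adjusted arm difference with its 95% confidence interval.

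The cost is one sentence and one degree of freedom (125 in place of 126 with 128 patients). It needs no new data, visits or patients, and the software already named can fit the model.

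Optionally, give a baseline-adjusted logistic estimate beside Fisher's test for yes/no achievement of these two goals, but only if there are enough non-achievers. With few of them the model may meet sparse data or separation, and Fisher's test should then stand alone.

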### Intervention fidelity and process evaluation

The efficacy of the ISDM programme may depend on the complex interaction between components (e.g. provider training and patient counselling strategies) and terms and conditions of the setting. Strategies to monitor and promote intervention fidelity [22] focus on study-design, provider training, delivery and receipt of intervention, and enactment of treatment skills (Table 3).

**Table 3 T3:** Intervention fidelity strategies

**Category **[22]	**Goals **[22]	**Elements of the ISDM study**
Design of study	• Ensure same treatment dose within conditions.	• Curriculum and media are standardised for both study arms
	• Ensure equivalent dose across conditions.	• Intervention and control-intervention are similar in framing, duration and structure
	• Plan for implementation setbacks	• For both intervention and control-intervention, two diabetes educators are trained to ensure the completion of the counselling sessions
Training providers	• Standardize training	• All diabetes educators are trained in standardised train-the-trainer sessions
	• Ensure provider skill acquisition	
	• Minimize “drift” in provider skills	• Educational material is standardised
		• Optimal patient counselling is demonstrated
	• Accommodate provider differences (adequate level of training, skills, experience and professional background)	• Providers practise counselling under supervision of a research fellow and subsequent feedback
		• Providers assess the patient knowledge questionnaire to ensure skill acquisition
Delivery of intervention	• Control for provider differences	• Counselling sessions are video-taped, constantly analysed, and fed back by a research fellow
	• Reduce differences within treatment	• Counselling protocol: deviation from curriculum (duration, material use, content, didactics) is documented
	• Ensure adherence to protocol	
	• Minimize contamination between conditions	
Receipt of intervention	• Ensure participant knowledge	• Questionnaire cards at the end of the counselling session. If there are difficulties in understanding, the diabetes educator discusses and corrects the answer and repeats the information
	• Ensure participant ability to use cognitive skills	
	• Ensure participant ability to perform behavioural skills	
Enactment of treatment skills	• Ensure participant use of cognitive skills	• Patients set individual treatment goals for heart attack prevention

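### Goal achievement is scored against a goal recorded only after counselling that elicits such goals in the ISDM arm and is not described as doing so in the control arm, so who can be scored may depend on treatment.

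*Protocol article*

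**What the plan says.** The protocol article's Objectives section sets the key secondary objective: to "determine if patients in the ISDM group achieve their individual treatment goals better than patients in the control-group". The Abstract narrows the key secondary outcome to the goal that the patient has prioritised.

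Under Secondary outcomes, "Fisher’s exact tests will be used to compare the groups regarding rates of individual goal achievement (yes/no"), for statin choice, smoking status, blood pressure and HbA1c. For the last two, success means reaching 80% to 120% of the goal. Unpaired t-tests also compare the individual differences between planned and achieved blood pressure and HbA1c.

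On where the goals come from:

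- **ISDM session.** The third of its three steps is "supporting to set individual goals regarding smoking cessation, glucose control, blood pressure control, and statin treatment". Table 3 lists goal-setting again under enactment of treatment skills: "Patients set individual treatment goals for heart attack prevention".
- **Control session.** "In contrast to the ISDM intervention, participants are guided through a counselling session about nutrition, sports, and stress coping". No step on the four scored goals is described.
- **Recording.** Data collection states: "The individual treatment goals regarding smoking cessation, glucose control, blood pressure control, and statin treatment are assessed after the counselling session". Table 2 places this at T1, with one item per goal, and the "patient’s prioritized treatment goal are documented on a standardised form". Neither place limits the form to one arm.

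The Data synthesis section gives intention-to-treat analysis, with multiple imputation of missing data if feasible.

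**The concern.** A yes/no on goal achievement, or a planned-minus-achieved difference, exists only for a patient with a recorded goal. That goal is recorded after randomisation, at the end of a session that works towards it in one arm and, as described, deals with other topics in the other. Having a scorable goal is therefore something the intervention can change.

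If the arms differ in how many patients have a goal, none of the obvious ways of handling the rest keeps the randomised comparison:

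- Counting no goal as not achieved lowers the control rate without any difference in what patients achieve.
- Excluding such patients compares nearly all of one arm with a self-selected part of the other.
- Multiple imputation fills in a value that exists but was not observed. A goal never set is not such a value.

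At stake is the between-arm conclusion on the key secondary objective. The primary outcome, knowledge, is not affected.

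**Working it through.** **The plan's own figure.** The Sample size section concerns knowledge only: difference 0.20, SD 0.4, two-sided 5%, 80% power.

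- Normal approximation: 2 × (1.96 + 0.84)² × (0.4/0.2)² = 62.7, so 63 per group. The t-distribution version gives 63.8, so 64 per group, as stated.
- 128/0.85 = 150.6, so 151, close to the 154 stated.

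No sample size or power is given for goal achievement, so there is no stated figure to reproduce on this point.

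**Inputs for the illustration**

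- From the article: 154 randomised and 15% lost, so 154 × 0.85 = 130.9, about 65 per arm; Fisher's exact test. The two-sided 5% level is taken from the Sample size section.
- Assumed, not in the article: true achievement p, equal in both arms, at 60% or 80%; every ISDM patient has a goal; a share s of controls has none.

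**Case 1: no goal counted as not achieved.** The control rate becomes p × (1 − s), and the spurious difference in favour of ISDM is p × s. Rejection probabilities are exact, summed over the two binomial distributions.

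| p | s | Control rate | Spurious difference | Fisher rejection |
|---|---|---|---|---|
| 60% | 0% | 60% | 0 points | 3% |
| 60% | 10% | 54% | 6 points | 8% |
| 60% | 20% | 48% | 12 points | 21% |
| 60% | 30% | 42% | 18 points | 45% |
| 80% | 0% | 80% | 0 points | 3% |
| 80% | 10% | 72% | 8 points | 14% |
| 80% | 20% | 64% | 16 points | 45% |
| 80% | 30% | 56% | 24 points | 80% |

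With s = 0 the test stays below its nominal 5%. All the excess comes from s.

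**Case 2: no-goal controls excluded.** Assume 60% achievement overall in the control arm, s = 30%, and 40% achievement among those excluded. The remaining controls then achieve (0.60 − 0.30 × 0.40)/0.70 = 0.686. ISDM stays at 60%, so the comparison shows a deficit of about 9 points for ISDM with no true effect.

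The two cases err in opposite directions, so the direction of the bias depends on the handling rule as well as on s.

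**The case against.** The strongest reply is that the article collects goals in both arms. T1 is the end of the counselling session, both arms have one, the form is not limited to ISDM, and the objective and both analyses presuppose goals in each group. Patients may also hold goals already. The Setting section says that educators develop individual care plans, eligibility requires earlier DMP education, and Table 3 speaks of current treatment goals. Two of the items, statins and smoking, are choices, so declining a statin may itself be a scorable answer.

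All of this stands. A reader might infer that only the ISDM session produces goals and that control patients cannot be scored. The documents do not support that reading. What they show is that only the ISDM session is described as eliciting these goals. A form records a goal but does not ensure that there is one, least of all a numerical blood pressure or HbA1c target or a stated priority.

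A second reply is that scoring a patient without a goal belongs in the full protocol or SAP, neither of which is shown. That is right for the rule itself, and its absence here is not the criticism. The difficulty is that no such rule restores the comparison if the arms differ in having goals, and that follows from the design as the article describes it.

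A third reply is that every driver of the illustration is assumed. That also stands: no figure in the article supports a no-goal share of 10% or 30%.

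Finally, the change in medication from T1 to T2 is already compared without reference to goals. That partly covers statin use, but not HbA1c, blood pressure or smoking.

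**Conclusion.** The point holds as a conditional one. Because goals are recorded only after a session that elicits them in one arm, having a scorable goal is a post-randomisation variable that treatment can change. If fewer controls than ISDM patients state a goal, neither the Fisher comparison nor the planned-versus-achieved comparison is unbiased under any of the usual handlings.

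The size cannot be determined from the article. It is nil if every control states a goal. The illustrated false-rejection rates, 8% to 14% at a 10% no-goal share and 45% to 80% at 30%, rest on 60% to 80% achievement, a goal for every ISDM patient, and no-goal controls counted as failures. They show how sensitive the result is to the share of patients with goals; they do not predict what will happen in this trial.

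The between-arm conclusion on the key secondary objective should therefore not rest on achievement of T1 goals alone.

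**What to change.** In Secondary outcomes:

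1. Add a between-arm comparison, in all randomised patients, of HbA1c, blood pressure and statin use at T2, each adjusted for its baseline value, and of smoking at T2 among baseline smokers. These outcomes are defined for every patient whether or not a goal was set, so multiple imputation can properly be applied to missing T2 values.
2. Report by arm the share of patients with a recorded T1 goal for each item, and the share with a prioritised goal.
3. Keep achievement of T1 goals as a reported result, and interpret it only alongside items 1 and 2.

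The cost is a little more analysis. Data collection already lists the baseline values, and Table 2 already lists the T2 values, so nothing new is needed from patients, including those already enrolled.

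The downside is that goal-free outcomes do not capture goals that the programme legitimately changes, which is why T1-goal achievement stays in the report. Recording goals before randomisation is optional. It would give both arms a common yardstick, but would score ISDM patients against goals that the programme is meant to let them revise.
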